### 1.3 Inclusion and exclusion criteria.

#### 1.3.1 Inclusion criteria

- 1) Age  $\geq 18$  years;
- 2) Admitted to ICU for the first time;
- 3) Expected ICU stay  $\geq 72$  hours;
- 4) Consciousness adequate to respond to at least three of these orders:  
"open/close your eyes", "look at me", "put out your tongue", "nod your head", "raise your eyebrows";
- 5) Informed consent of patients or their agents

#### 1.3.2 Exclusion criteria

- 1) Incomplete limbs;
- 2) Pre-existing primary systemic neuromuscular disease (e.g., Guillain Barre,

myasthenia gravis, amyotrophic lateral sclerosis);

- 3) Intracranial or spinal process affecting motor function;
- 4) Had gastrointestinal surgery in one month;
- 5) Hyperthyroidism and other endocrine diseases affecting nutrition and metabolism;
- 6) Pregnant;
- 7) Has terminal cancer, expected death or extremely poor prognosis;
- 8) No expectation for any nutritional intake within the subsequent 48 hours

## **2. Study design and intervention**

### **2.1 Study design**

This is a randomized controlled trial conducted from May, 2020 to April 2021 for ICU patients, aiming at reduce the occurrence of ICU-AW.

### **2.2 Intervention**

All three groups will receive standard ICU care, which includes conventional nutrition support and physiotherapy. With the exception of patients in the ENM group, all patients in the other two groups will receive conventional nutrition therapy. The contents of nutritional support nursing, laboratory index testing, feeding speed, nutritional targets and nutrient composition are completely consistent among the three groups. Nutritional targets will be measured by weight-based equation 20-25 kcal/kg/d.

*2.2.1 Control group.* Participants in the control group will only receive standard ICU care. The usual care strategy is as follows:

1. Closely monitor vital signs, observe any changes in illness; regularly measure

central venous pressure (CVP), arterial blood pressure and blood gas analysis;

identify and manage abnormal conditions in a timely manner.

2. Maintain indoor temperature and humidity at suitable levels and keep the bed clean and tidy.
3. Carefully manage all types of tubes.
4. Perform oral nursing care, perineal care, bedsore nursing; turn patient over every 2 h.
5. Invite the occupational therapist, according to the ICU doctor's order, to perform rehabilitation exercise therapy for certain patients with no fixed time, method, or frequency, as described above. The present conventional methods include massaging muscles; passive, active assisted, or active mobilization; and bed positioning and maintenance of orthostatism. Nevertheless, the type of therapy will not be defined in advance, but instead will be at the discretion of the attending physiotherapist and will not have a pre-established routine.
6. Provide nutritional support as ordered by the doctors. Energy requirements are calculated as 20 to 25 kcal/kg/day. Different doctors have different strategies of nutrition support, such as initiation time, route of nutrition, and inclusion or exclusion criteria for nutrition therapy.

*2.2.2 Early mobilization group.* Patients in the EM group will receive early mobilization intervention twice daily in addition to standard treatment. Physiotherapists, nurses responsible for the patients, and the study researchers will collaborate to implement early mobilization intervention based on the patient's Barthel Index (BI) score starting within 24 h of ICU admission, twice daily. The early

mobilization intervention is created by the research team based on data in the academic literature.

*Mode 1: Wholly compensatory system*

BI score: <40.

Exercises: Passive movement. Perform muscle kneading and passive movement of extremities twice per day. Exercise in the main direction of the joints of each limb will be repeated 10 times, such as flexion and extension of upper limbs and fingers; flexion, extension, radial deviation and ulnar deviation of the wrist joint; flexion, extension, abduction and adduction of the elbow joint; and flexion, abduction, internal rotation and external rotation of the shoulder joint.

*Mode 2: Partly compensatory system*

BI score:  $\geq 40$  and <60.

Exercises: Passive movement combined with active movement. The bed-head angle will be increased to 30-45°, and the passive exercise described in mode one will be repeated 5 times with each limb. Clenching fists for 10 s and the ankle pump exercise for 15 s will both be performed 20 times per side. Active sitting in bed will be performed for 20 min. If the patient is able to finish the above exercises, he or she will perform active movement of the joints of the extremities while on the bed; that is, chest expansion and abduction of the upper limbs (arms) and kicking of the lower limbs (legs), all repeated 30 times. Patient will then perform assisted bedside sitting for 20 min. Patients capable of these movements will progress to assisted standing against the bed for 5 min.

*Mode 3: Supportive-educative system*

BI score:  $\geq 60$ .

Exercises: Active movement. Patient will perform active bedside sitting for 10 min, and active standing against the bed for 10 min. Patients who can achieve these will shift to standing independently for 5 min, then marking time for 10 min.

The therapy session will be paused or terminated if the patient:

- Has a heart rate above 130 bpm/min or below 60 bpm/min
- Has a heart rate decreasing by more than 20% while resting, with irregular rhythm
- Has a systolic blood pressure above 180 mmHg or below 90 mmHg, or mean arterial pressure above 100 mmHg or below 60 mmHg
- Has a blood oxygen saturation below 88%
- Has a respiratory rate below 5 breaths/min or above 40 breaths/min
- Receives mechanical ventilation, and the oxygen concentration is above 60%; or the positive end expiratory pressure (PEEP) is above 10 cmH2O, and the patient is ventilated by control mode (CMV)

*2.2.3 Early mobilization combined with early nutrition group.* In addition to ICU routine nursing and the early mobilization intervention, patients in the ENM group will receive an early medical nutrition program based on the 2018 European Society for Clinical Nutrition and Metabolism (ESPEN) guideline [13] and the academic literature; this will be initiated within 48 h of ICU admission.

Patients with a Nutritional risk screening (NRS 2002) score  $\geq 3$ , which indicates the need for nutrition support [3], will receive early medical nutrition therapy consisting of early oral nutritional supplements and artificial nutrition (enteral

nutrition, parenteral nutrition) [4]. Oral feeding is preferred over artificial nutrition when the patient is able to eat independently. Patients who cannot take food by mouth will be given early persistent EN within 48 h. Postoperative patients will be supplied with EN within 24 h after surgery. Early enteral nutrition (EN) is preferred over early parenteral nutrition (PN). Patients with severe malnutrition (grade C of the subjective global assessment (SGA)) [5] or with high nutrition risk (NRS 2002 score  $\geq 5$ ) [3] will receive early progressive low-dose parenteral nutrition (PN) if they have EN contraindications. At the early stage of the acute phase of injury (within three days), patients will be provided with low-calorie nutrition of no more than 70% of their measured energy consumption. After three days, the amount of calories given should be increased to 80% of the measured energy consumption. Patients allocated to the ENM group will have energy requirements calculated as 20 to 25 kcal/kg/day.

### 3. Outcomes

Table 1. Outcome assessment.

| Outcomes                           | Timepoint                                                     |
|------------------------------------|---------------------------------------------------------------|
| Baseline characteristics           | Enrolment                                                     |
| BI                                 | Enrolment, every 24 hours following enrollment, ICU discharge |
| MRC sum-score                      | Enrolment, ICU discharge                                      |
| SOFA score                         | Enrolment, every 24 hours following enrollment, ICU discharge |
| Time of ICU stay                   | ICU discharge                                                 |
| Duration of mechanical ventilation | ICU discharge                                                 |
| ICU mortality                      | ICU discharge                                                 |

BI = Barthel index, ICU = intensive care unit, ICU-AW = intensive care unit-acquired weakness, MRC = Medical Research Council, SOFA = Sequential Organ Failure Assessment.

### 4. Statistical analysis

Statistical analyses will be conducted by an independent statistician using SPSS Statistics software (version 20.0) adopting two-tailed tests, with *p* values below 5%

indicating statistical significance.

Continuous data were expressed as mean  $\pm$  standard deviation (normal variables) or medians (non-normal variables), and categorical data were presented as number (%). Normal variables among three groups were compared by one-way ANOVA analysis, non-normal variables and ranked data with nonparametric Kruskal Wallis test, and categorical data (except for ranked data) as well as their pairwise comparisons with Chi-squared test. The data of three groups at different time points will be compared by repeated measurement analysis of variance.

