### 1.1.2 Group allocation

Simple random grouping with Excel will be applied in this trial.

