### 1.2 Sample size calculation

With a power of 90% and 2-sided 5% level of significance, 49 participants per group (147 total) will be needed to detect a significant between-group difference in the primary outcome, as calculated by PASS (version 11.0.7) and allowing for up to 10% attrition at ICU discharge (i.e., 132 participants with complete data). The estimated effect size is based on the incidence of ICU-AW at ICU discharge (early mobilization group=33.1%, control group=51.9%) reported in a meta-analysis of early mobilization interventions for critically ill patients [1] as well as the findings of Chen (2017) in a clinical trial (15.9%) [2].

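### Enrolment MRC is collected but none of the planned tests uses it as a covariate, so the ICU-AW and MRC comparisons give up precision that is already available

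*Protocol*

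**What the plan says.** - Protocol section 1.2 bases the effect size on the "incidence of ICU-AW at ICU discharge": 51.9% in control, 33.1% with early mobilization, and a third rate of 15.9% not tied to an arm. It concludes: "With a power of 90% and 2-sided 5% level of significance, 49 participants per group (147 total) will be needed". After 10% attrition, 132 are expected to have complete data.
- Table 1 in section 3 lists the MRC sum-score at "Enrolment, ICU discharge".
- Section 4 gives the methods: "Normal variables among three groups were compared by one-way ANOVA analysis"; Kruskal-Wallis for non-normal and ranked data; chi-squared for other categorical data and their pairwise comparisons; repeated-measures ANOVA for data at several time points. No covariate is named for any of them.
- Section 1.1.2 describes the allocation: "Simple random grouping with Excel will be applied in this trial". No stratification is mentioned.
- Section 1.3.2 excludes primary neuromuscular disease, intracranial or spinal processes affecting motor function, and incomplete limbs. A low enrolment MRC is not an exclusion, and the protocol gives no MRC cut-off for ICU-AW.

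**The concern.** Strength at entry is likely to predict strength at discharge. It is measured in every patient before treatment can act, and simple randomisation in groups of 49 does nothing to balance it. Yet the comparison of ICU-AW is a plain chi-squared test.

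MRC, measured twice, falls under repeated-measures ANOVA. With two time points its group-by-time term is a test of change scores. Its group main effect averages the pre-treatment value with the discharge value, which halves a difference present only at discharge. Neither is the efficient baseline-adjusted comparison.

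What is at stake is power, mainly in the adjacent pairwise contrasts, where it is low. A separate question is how patients who are weak at enrolment enter a count of acquired weakness.

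**Working it through.** **Inputs.** From section 1.2: rates 0.519, 0.331 and 0.159 (the last read as the combined group), two-sided 5%, power 90%, 132 evaluable, so 44 per group. The protocol gives neither the enrolment-discharge correlation r nor the share of patients weak at entry. Both are assumed over a range.

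**1. The plan's own figure.** Three-group chi-squared test, 2 degrees of freedom:
- Mean rate = (0.519 + 0.331 + 0.159)/3 = 0.3363.
- w² = mean squared deviation / [0.3363 × 0.6637] = 0.02162/0.2232 = 0.0968, so w = 0.311.
- N for 90% power = 131, taken as 132 (power 0.903). 132/0.9 = 146.7, so 147, or 49 per group.

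The 147 reproduces as a three-group comparison, and this point does not make it wrong. With 44 per group, the analytic unadjusted pairwise power is 43% for early mobilization v control, 47% for combined v early mobilization, and 96% for combined v control.

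**2. ICU-AW with adjustment.** Simulation: enrolment and discharge strength are bivariate normal with correlation r, and a patient is weak at discharge below the threshold that gives the planned rate. The unadjusted chi-squared test is set against the likelihood-ratio test for group in a logistic model with the enrolment value. Where two figures stand, they come from two independent runs (one with 12,000 trials per setting).

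| Comparison, 44 per group | Unadjusted | r = 0.3 | r = 0.5 | r = 0.7 |
|---|---|---|---|---|
| Combined v early mobilization | 47–49% | 49–50% | 53–55% | 63% |
| Early mobilization v control | 43–45% | 46–49% | 51–53% | 59–60% |
| Three groups | 92% | 93% | 96% | 98% |

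Type I error was about 5–6% for both tests. The slight excess over 5% may explain part of the small gain at r = 0.3.

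**3. MRC score.** With equal variance σ² at both times, the variance factors are 2 − 2r for the change contrast and 1 − r² for ANCOVA. Their ratio is (1 − r²)/(2 − 2r) = (1 + r)/2 = 0.65, 0.75 and 0.85, so ANCOVA variance is 35%, 25% and 15% lower. The difference detectable with 90% power at pairwise 5% is (1.960 + 1.282) × √(2/44) = 0.69 SD, times the square root of the factor:
- change contrast: 0.82, 0.69 and 0.54 SD;
- ANCOVA: 0.66, 0.60 and 0.49 SD.

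**4. Weakness already present at entry (separate from adjustment).** Suppose the planned rates describe new weakness, and a share q is weak at entry and stays weak in every arm. The observed rate is then q + (1 − q)p. Three-group power with 132 patients is 90% at q = 0, 85% at 5%, 80% at 10% and 68% at 20%. If the planned rates already include such patients, nothing is lost against the plan.

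**The case against.** The strongest reply is that nothing here is invalid. Randomisation balances entry strength in expectation, and chance imbalance is already covered by the test's error rate. The simulated type I error bears this out. The three-group comparison that matches the sample size has about 90% power without adjustment. At r = 0.3 the gain is only a few points, and covariates may be named in an analysis plan that is not shown. All of this stands, and it limits the point to precision. It does not remove it: section 4 names its tests outright, and a baseline value that is already collected is left unused as a covariate.

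Three stronger readings are tempting, and the protocol does not support them.
- A reader might infer that weakness present at entry counts as acquired *because* MRC is not adjusted for. That does not follow: a covariate reclassifies nobody. Since the protocol states no ICU-AW definition or cut-off, how such patients are counted is itself an inference from the eligibility criteria and timing. Several causes of prior weakness are excluded.
- A reader might infer that chance imbalance biases the result. It adds noise, not systematic error.
- A reader might infer that adjustment rescues the adjacent pairwise contrasts. Even at r = 0.7 they reach only about 60–63%; their low power is mainly a matter of sample size.

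Nor is a discharge-only ANOVA the right benchmark for MRC. Against it ANCOVA would save 9%, 25% and 49% of the variance, but section 4 sends data at several times to repeated-measures ANOVA, so the relevant savings are 35%, 25% and 15%.

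**Conclusion.** The point holds as a loss of precision. The planned tests are valid, but they leave enrolment MRC out as a covariate. For ICU-AW, adjustment gains roughly 1 to 4 points of pairwise power at r = 0.3, 4 to 10 at r = 0.5 and 14 to 17 at r = 0.7, and about 1 to 6 points for the three-group test. For MRC it removes 15–35% of the variance of the change contrast. These sizes rest on the assumed correlations, on a bivariate normal model for strength, and on reading 15.9% as the combined-group rate. Weakness already present at entry is a separate, conditional concern that adjustment does not settle. The change is worth making because it is nearly free, not because the planned analysis would mislead.

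**What to change.** Amend section 4 as follows:
- **ICU-AW at discharge (primary).** Logistic regression on group and enrolment MRC sum-score, reporting adjusted risk differences with 95% confidence intervals. Keep the chi-squared test as supportive.
- **MRC and BI at discharge.** ANCOVA on group and the enrolment value of the same score.
- **Sensitivity analysis.** Repeat the ICU-AW comparison in patients not weak at enrolment, using the same MRC cut-off as at discharge. The cut-off has to be written down for this.

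No new data or patients are needed: Table 1 already has MRC and BI at enrolment. The cost is a little more analysis work, a model assumption, and little return if the correlation turns out near 0.3. The change should be fixed before outcome data are seen by group.

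### ICU stay and ventilation time are compared by tests that cannot use the enrolment SOFA score: a loss of precision in non-primary outcomes, not a bias

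*Protocol*

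**What the plan says.** Section 3, Table 1 lists SOFA with the timing "Enrolment, every 24 hours following enrollment, ICU discharge". ICU stay and "Duration of mechanical ventilation" appear in the same table, each recorded once, at ICU discharge.

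Section 4 chooses tests by type of variable: "Normal variables among three groups were compared by one-way ANOVA analysis", and Kruskal-Wallis for non-normal or ranked data. Repeated-measures ANOVA is kept for data taken at several time points, which these two durations are not. The protocol names no covariate-adjusted model.

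On allocation, section 1.1.2 says only: "Simple random grouping with Excel will be applied in this trial". It mentions no stratification or blocking.

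Section 1.2 sizes the trial on ICU-AW incidence: "49 participants per group (147 total) will be needed", "allowing for up to 10% attrition at ICU discharge", which leaves "132 participants with complete data".

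**The concern.** Entry is broad: adults on a first ICU admission, expected to stay at least 72 hours and able to respond to simple orders. Severity at entry can therefore vary widely between patients. If enrolment SOFA predicts how long patients stay or are ventilated, two things follow from leaving it out.

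- The variation it could explain stays in the error term, so intervals are wider and power is lower than the collected data allow.
- If one arm happens to be sicker at entry, that difference passes into the observed contrast for these outcomes. Unstratified allocation does nothing to make such a draw less likely.

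The trial was not sized for these two outcomes, so precision that costs no patients is worth having. A rule fixed in advance also removes the temptation to decide on adjustment after seeing the baseline table.

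**Working it through.** **1. The plan's own figure.** Inputs from section 1.2: 90% power, two-sided 5%, ICU-AW rates 51.9% (control), 33.1% (EM) and 15.9%. The text does not name the arm for the last rate; it is taken here as the combined arm. For a three-group chi-square test with 2 df, the mean rate is 0.336 and the effect size w is 0.311. Power of 90% needs N = 131, so 44 per arm (132), where power is 90.3%. Then 44/(1 − 0.10) = 48.9, so 49 per arm (147). The stated size reproduces. It rests on a binary outcome, so nothing below changes it.

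**2. Chance imbalance in enrolment SOFA.** In SD units, the difference between two arm means has standard error √(2/n).

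| | n = 49 per arm | n = 44 per arm |
|---|---|---|
| √(2/n) | 0.202 | 0.213 |
| P(a given pair differs by > 0.3 SD) | 14% | 16% |
| P(some pair of the three differs by > 0.3 SD) | 30% | 34% |

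These figures treat the arms as equal in size, which simple randomisation does not guarantee.

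**3. What an imbalance does to the estimate.** Shift = correlation × gap. At an assumed correlation of 0.4, a 0.3 SD gap moves the contrast by 0.4 × 0.3 = 0.12 SD. That is 0.12/0.202 = 0.59 standard errors of a pairwise difference at 49 per arm.

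**4. Validity of the unadjusted test.** In 6,000 simulated trials with 44 per arm and no treatment effect, one-way ANOVA rejected in 4.7% at correlation 0.3 and in 4.7% at 0.5. The overall level is kept. In the 6 to 7% of trials where control and combined arms differ by more than 0.4 SD in SOFA, rejection rises to about 7% (correlation 0.3) or 13% (0.5).

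**5. Precision gained by adjusting.** Residual variance becomes (1 − ρ²) times the unadjusted variance, and 132 complete cases act like 132/(1 − ρ²). For power, assume effects of 0, 0.3 and 0.6 SD in control, EM and combined arms and 44 per arm. The noncentrality of the F test is 44 × (0.3² + 0 + 0.3²) = 7.92, and adjustment divides it by (1 − ρ²). The denominator df are 129 for ANOVA and 128 for ANCOVA.

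| Assumed ρ | Variance removed | 132 act like | ANOVA power | ANCOVA power |
|---|---|---|---|---|
| 0.1 | 1% | 133 | 70.2% | 70.7% |
| 0.2 | 4% | 138 | 70.2% | 72.1% |
| 0.3 | 9% | 145 | 70.2% | 74.5% |
| 0.4 | 16% | 157 | 70.2% | 78.1% |
| 0.5 | 25% | 176 | 70.2% | 82.8% |

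The gain is 0.5 to 1.9 points at 0.1 to 0.2, and 4.3, 7.9 and 12.6 points at 0.3, 0.4 and 0.5.

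**6. The same on ranks.** Simulated at 44 per arm, Kruskal-Wallis against rank ANCOVA gives about 68 to 72%, 67 to 75% and 66 to 78% at 0.3, 0.4 and 0.5. The rank version keeps a similar gain.

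**The case against.** The strongest reply is that nothing here is an error. Under randomisation the unadjusted tests are valid, and their 5% level already allows for chance imbalance. This stands. A reader might infer that a sicker arm biases the comparison or inflates its error rate. Step 4 shows that it does not, averaged over randomisations; only the error conditional on a large imbalance rises, and such imbalances are uncommon.

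Second, the protocol does not say that SOFA predicts either duration, and gives no correlation, SD or effect size for them. This also stands. The size of the gain is therefore conditional, and at low correlations there is almost none.

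Third, the benefit is easily exaggerated. Setting Kruskal-Wallis against a parametric ANCOVA on normal data with 49 per arm shows about 72% rising to 79, 81 and 86% at correlations 0.3, 0.4 and 0.5. Part of that comes from leaving ranks, since the same comparison shows about 2 points at correlation zero. The like-for-like figures at the expected 44 complete cases per arm are the fair ones.

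Fourth, a log-days model is undefined for patients with no ventilation, and the inclusion criteria do not require ventilation. This stands and limits the fix.

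Finally, adjusted models are often left to an analysis plan, which may exist but is not shown. The absence of such a model from a protocol would be no finding by itself. Section 4, however, does fix the tests for these outcomes, and the point is about that stated choice.

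**Conclusion.** The point holds as a low-severity matter of efficiency, confined to ICU stay and ventilation time. Section 4 fixes tests that cannot use a baseline severity score already collected on every patient, and allocation does not balance it. The cost is lost precision, and an estimate that carries whatever severity imbalance the single randomisation produces.

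The imbalance figures in step 2 assume only approximately normal arm means and equal arms. The power figures rest further on the assumed correlation, the assumed 0.6 SD effect with EM halfway, and normality on the analysis scale. None of these is in the protocol.

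The protocol does not support reading this as a flaw in the primary result. The ICU-AW comparison is not touched, and the stated 147 reproduces and stands.

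**What to change.** In section 4, pre-specify for these two outcomes a three-arm comparison adjusted for enrolment SOFA:

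- ventilation time: rank ANCOVA, because zero days are possible;
- ICU stay: rank ANCOVA or a linear model on log days, with the choice named in advance.

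Report combined versus EM, combined versus control and EM versus control from that model. Keep the unadjusted ANOVA or Kruskal-Wallis as a supporting analysis. Fix the covariate before any data are seen by arm.

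The cost is a sentence or two in section 4 and one model term; no new data, visits or patients are needed. The downsides are an assumption of linearity in SOFA on the chosen scale, and rank-scale contrasts that are harder to interpret than a difference in days. Adjustment also does nothing about durations cut short by ICU death, which is a separate matter.

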# Study Protocol

**Title:** Effect of early mobilization combined with early nutrition on acquired weakness in ICU patients

**Director:** [name]

**Purpose:** This study adopted Orem self-care theory as the framework of early mobilization (EM) intervention, and European Society for Parenteral and Enteral Nutrition (ESPEN) guideline (2019) of early nutrition intervention, aiming to construct an innovative intervention strategy against intensive care unit-acquired weakness (ICU-AW), and to investigate whether the participation in early mobilization combined with early nutrition (EMN) program in the ICU is better than EM alone or routine ICU care.

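### Section 4 does not tie the pairwise chi-squared tests to the three-group test; run as written at 5% each, they carry a family-wise error of about 12% on ICU-AW

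*Protocol*

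**What the plan says.** Protocol section 4 applies one threshold to all tests, "adopting two-tailed tests, with *p* values below 5" per cent. The sentence that assigns tests to types of data begins with the three-group comparison, "Normal variables among three groups were compared by one-way ANOVA analysis", and ends with "categorical data (except for ranked data) as well as their pairwise comparisons with Chi-squared test". The chi-squared test therefore serves both the three-group comparison and the pairwise comparisons of a categorical outcome such as ICU-AW. No order of testing and no adjusted level is given.

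The purpose statement asks whether EMN "is better than EM alone or routine ICU care", which names two contrasts. Section 1.2 sizes the trial "With a power of 90% and 2-sided 5% level of significance" for a between-group difference in the primary outcome, with the effect size taken from the incidence of ICU-AW at ICU discharge. It concludes that "49 participants per group (147 total) will be needed", "allowing for up to 10% attrition at ICU discharge (i.e., 132 participants with complete data").

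**The concern.** A three-group chi-squared test has two degrees of freedom and no direction. It cannot say whether EMN beats EM, or whether EMN beats routine care. The conclusion the trial is after must come from the pairwise tests, and the protocol chooses those tests, their method and their threshold. Read literally, a pairwise p value of 0.04 counts as significant whatever the three-group test shows. The 5% error rate of the three-group test then does not protect the pairwise conclusions, and a false claim about one pair of arms is more than twice as likely as the nominal level suggests.

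**Working it through.** **Inputs.** From section 1.2: two-sided 5%, 90% power, 49 per group, 132 complete (132/3 = 44 per group), ICU-AW rates of 51.9% (control) and 33.1% (EM), and a third rate of 15.9% from a single clinical trial. That 15.9% belongs to the EMN arm is an assumption; the protocol does not say so.

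**Step 1: reproduce the sample size.** Mean rate = (0.519 + 0.331 + 0.159)/3 = 0.3363. The effect size squared is the mean squared deviation over p(1 − p): 0.02161/(0.3363 × 0.6637) = 0.0968, so w = 0.311. For the three-group chi-squared test (2 df, 5%), the noncentrality at N = 132 is 132 × 0.0968 = 12.78 and the power is 90.3%. The smallest N for 90% is 131, which rounds up to 44 per group. Then 132/0.9 = 146.7, that is 147. The stated figures reproduce.

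The two-sided 5%, 90% pairwise calculations tried do not give 44 per group: control versus EMN needs 35 (40 with continuity correction), EM versus EMN 130, control versus EM 144. The trial therefore appears to be sized on the three-group test.

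**Step 2: family-wise error of three ungated pairwise tests, equal true rates.**
- Large-sample value: the probability that the range of three independent standard normals exceeds 1.96 × √2 = 2.77, which is 12.2%.
- Independence would give 1 − 0.95³ = 14.3%, but the three tests share arms and are correlated.
- For the two EMN contrasts only, the large-sample value is 9.0%.

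Simulation at 44 per group (uncorrected Pearson chi-squared, at least 400,000 trials per row; error about 0.1 point):

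| Common true rate | Any of 3 pairwise | Either EMN contrast | Any pairwise, gated |
|---|---|---|---|
| 15.9% | 13.0% | 9.7% | 5.0% |
| 33.1% | 13.1% | 9.7% | 5.1% |
| 33.6% | 13.2% | 9.8% | 5.1% |
| 42.5% | 12.0% | 8.9% | 4.9% |
| 51.9% | 10.8% | 8.1% | 4.9% |

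At 49 per group the ungated range is 11.6% to 13.2% and the gated range 4.9% to 5.2%.

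**Step 3: why the gate suffices.** With three groups there are three pairwise null hypotheses. If any two are true, all three are true, so every intersection is the global null. Testing the global null at 5%, and then each pair at 5%, is a full closed test. When only one pair is truly equal, the simulated false-positive rate for that pair under the gate is 4.3% to 5.4%; the small excess over 5% comes from the discreteness of the chi-squared test.

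**Step 4: power at 44 per group, rates 51.9/33.1/15.9%.**

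| Contrast | Ungated 5% | Gated 5% | Bonferroni (5%/3) |
|---|---|---|---|
| EMN vs control | 96% | 92% | 90% |
| EMN vs EM | 48.3% | 47.7% | 30% |
| EM vs control | 43% | 43% | 27% |

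**The case against.** The strongest reply is that the protocol never says the pairwise tests run regardless. The same sentence contains the three-group test, the sample size matches that test, and if pairwise tests follow only when it is significant, the error rate is already about 5%. The SAP was not available for this review and may fix the order. This stands in part. The order is unstated, not decided, so a reader who infers that the trial's error rate is 13% goes too far: that is the top of the range, it applies only to ungated tests, and the three-group test on ICU-AW holds 5%. What remains is that the written rule attaches the 5% threshold to the pairwise tests without condition.

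A reader might also infer that one win, over either EM or routine care, counts as success. The purpose statement does not settle this. It can equally mean better than each comparator, and if both contrasts had to be significant, the inflation of an EMN claim would not arise.

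Nor do the documents support three wider charges:
- **That no primary outcome is identified.** Table 1 has no ICU-AW row, but section 1.2 ties the primary outcome to ICU-AW at ICU discharge.
- **That the MRC sum-score lacks a suitable analysis.** It is measured at two time points and can fall under the repeated-measures analysis of variance in section 4.
- **That pairwise follow-up after ANOVA or Kruskal-Wallis is wrongly omitted.** This is detail that an SAP commonly supplies.

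**Conclusion.** The point holds in conditional form. Without a gate, the family-wise false-positive rate on ICU-AW under equal true rates is at least double the nominal 5%, and for the two EMN contrasts it is still well above 5%. The error figures assume uncorrected chi-squared tests and common true rates between 15.9% and 51.9%; they do not depend on which arm 15.9% belongs to. The sample-size reproduction and the power figures do. This is a cheap improvement to the wording of section 4. It does not show that the design or the sample size is wrong.

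**What to change.** Add to section 4: *For ICU-AW at ICU discharge, the three-group chi-squared test is carried out first at the two-sided 5% level. Pairwise chi-squared tests, each at two-sided 5%, are interpreted only if that test is significant.*

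The cost is two sentences and no extra patients. At the planning rates the power loss is about 4 points for EMN versus control and less than 1 point for EMN versus EM. The loss depends on the true rates and would differ under other patterns. The gate is preferable to Bonferroni here, because Bonferroni would cut EMN-versus-EM power from 48% to 30%. The gate does not cure the low power of that contrast, which is below 50% with or without it. If the SAP already states this order, the protocol need only refer to it.
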